## Abstract

**Background:**

Violence in families affects children. Exposure to violence is seen as child abuse. Figures show that about one third of children exposed to violence become victim or perpetrator in their adult life: known as intergenerational transmission. Violence also affects sexual and reproductive health. To prevent problems in adult life, children need help and support. However, while trying to protect their parents, children often do not seek help, or perceive the threshold as too high. Since almost all children of the current generation have access to the internet, an online intervention will make help better available for this target group. In 2011, an internet-based self-support method for children, adolescents and young adults exposed to family violence was developed in the Netherlands: “Feel the ViBe”. The intervention was developed in close collaboration with the target group. This article describes the protocol of the RCT to study the effectiveness of this intervention.

**Methods/design:**

This study is a randomized controlled trial using the method of minimization to randomize the participants in two parallel groups with a 1:1 allocation ratio, being an intervention group, having access to “Feel the ViBe” and usual care (UC), and a control group, having access to minimally enhanced usual care (mEUC) followed by access to the intervention after twelve weeks. Outcomes are measured with questionnaires on PTSD symptoms, mental health and sexual and reproductive health. Routine Outcome Measurement (ROM) will be used to measure a direct effect of participating in the intervention. Data from a web evaluation questionnaire (WEQ), user statistics and qualitative analysis of online data will be used to support the findings. To compare results Cohen’s d effect sizes will be used.

**Discussion:**

A RCT and process evaluation will test effectiveness and provide information of how the effects can be explained, how the intervention meets the expectation of participants and which possible barriers and facilitators for implementation exist. A qualitative analysis of the data will add information to interpret the quantitative data. This makes “Feel the ViBe” unique in its field.

**Trial registration:**

The Netherlands National Trial Register (NTR), trial ID NTR3692.

## Background

Violence in families mostly affects women and children. Cross-sectional surveys in General Practice show that the prevalence of family violence for women between 16–65 years of age is estimated at 30-41% [1-3]. The WHO defines family violence as any behaviour within an intimate relationship that causes physical, sexual or psychological harm, including acts of physical aggression, sexual coercion, psychological abuse and controlling behaviours. This definition covers violence by both current and former spouses and partners [4]. The Netherlands Youth Institute (NJI) includes in their definition that other family members, including children, are, directly or indirectly, affected by the exposure to the violence and considers it as child abuse [5]. In 2006, in 60% of the cases of family violence in Dutch women registered by the police, there were children living at home, and in most cases they were exposed to the violence against their mothers. This leads to an estimate of 15.340 children in the Netherlands exposed to family violence [6]. In 2008, 23% of the contacts with the Dutch Child Abuse Authority (AMK) concerned exposure to family violence [7].

Family violence contributes to significant morbidity, such as depression and anxiety disorders [8]. Children in families where violence occurs are in a very difficult position, often supporting the victim, trying to protect him or her, instead of being protected themselves. Their feelings and comprehension of ‘safety’ as well as their immediate safety are highly under pressure. Repeated subjection to violence and the interfamilial character increase the chance of developing mental health or behavioural problems. These children are as much at risk for long term negative consequences as children who are abused themselves. The consequences are diverse: mental health problems, such as affective and depressive disorders and suicide attempts, educational problems, such as school drop-out, behavioural problems, substance/drug abuse and risk taking behaviour. They also have a one-in-three chance of becoming either victim or abuser in their adult life. This is called intergenerational or transgenerational transmission [9-14]. Several theoretical models underlie these findings. Ehrensaft et al. and Carpenter & Stacks both give an extensive overview of these models, including the social learning theory of Bandura [11,15,16]. This theory states that children learn new behaviour by observing and imitating significant others, called modelling. If children are exposed to violence, they learn that violence is an acceptable or effective means of resolving conflicts with the partner. Other theories are the betrayal trauma theory [17] and the attachment theory: parenting stress can impact internalizing and externalizing behaviour and lead to increased stress and symptoms of posttraumatic stress disorder (PTSD) [18-20].

Family violence also influences reproductive and sexual health. A systematic review by Coker [21] addressed family violence and sexual health. Family violence was consistently associated with sexual risk taking, unplanned pregnancy or induced abortion, sexually transmitted disease (STD) and sexual dysfunction [21]. There is hardly any research studying the consequences of exposure to family violence on reproductive and sexual health issues in children and adolescents. The few studies focusing on adolescents exposed to violence at home, found an association with sexual risk behaviour, having sex before age 15, multiple partners, having a STD, unplanned pregnancy, and alcohol/drug use in relation to sexual activities [9,22-26].

In order to prevent intergenerational transmission, mental health problems and sexual/reproductive risk behaviour in adult life, it is important that early support for children, adolescents and young adults exposed to family violence is available. Support, however, is scarce. Most of the preventive interventions in the Netherlands are regional, do not offer specialized care or have a high threshold. Interventions specifically aimed at children and adolescents exposed to family violence are mostly group therapy. These interventions all require involvement and/or consent of parent(s), regular mental healthcare and/or need a referral from the GP or Child Protection agency. Knowing that these children often support their mother by trying to protect her, instead of being protected, they are not likely to seek help for themselves unless their mother is already receiving help [27,28]. Unfortunately, women who face family violence are often too afraid to seek help and mothers with children at home are even more vulnerable since they try to protect their children. Trying to maintain the family, they do not leave the abusive partner in many cases. Above that, regular health services frequently fail to deliver appropriate support due to long waiting lists and because they do not meet women’s needs [29,30]. The surroundings, abusers, mothers and GP’s are in most cases not aware of the long-term consequences of exposure to family violence for children [3]. Therefore, children and adolescents exposed to family violence are difficult to reach. Moreover, evidence is lacking on the effects of preventive interventions and the possible role of primary health care [31].

To prevent intergenerational transmission and negative effects on reproductive and mental health, a low-threshold support method is needed for children, adolescents and young adults exposed to family violence. Children and adolescents of the current generation often rely on the internet as source of information and to maintain their social contacts. In the Netherlands, 93% of the children age 6–18 use the internet and 78% use social networking sites. Of the adolescents, age 12–18, 96% have a mobile phone. After contacting friends in real life, the internet and their mobile phone are the most important sources for adolescents age 12–18. A good website according to adolescents age 12–18, gives them reliable information, provides social support and is safe [32,33]. Considering this, it is to be expected that children who are exposed to family violence will search for information on the internet. Although general information on sexual and reproductive health and general help, for example the ‘Kindertelefoon’ (‘Children’s telephone’: support for children by phone and chat), is available online, there is hardly any specific information on what to do. An internet-based self-support method can be a low-threshold method to give support. E-health is still a commencing method and most interventions available online are based on assumptions and literature instead of including the wishes, needs and demands of the target group. Because of constraints from ethical boards when it concerns minors, most of these interventions are not evaluated well. Peer support and peer education, however, are researched extensively and are nowadays recognized as effective methods to change behaviour [34-37]. Furthermore, social support has proven to be effective in adults exposed to violence and is associated with good mental and physical health outcomes [38,39].

In 2011 “Young People, Adult worries” started with the development of a new internet-based self-support method for children, adolescents and young people exposed to family violence. Based on opinions from the target group, experts and literature, “Feel the ViBe (Violence Beaten)” was developed. “Feel the ViBe” is intended as a freely available, low-threshold stand-alone intervention for children, adolescents and young people who are exposed to family violence. The primary goals are to provide (peer)support and information. If “Feel the ViBe” is successful, this may have large impact on the traditional healthcare, possibly leading to more help offered and less costs.

This study protocol briefly describes the development of the intervention, which took place in 2011, followed by the protocol for the effectiveness study.

### Primary objective

•To study the effectiveness of the internet-based self-support method “Feel the ViBe”.

### Secondary objectives

•To explore knowledge about sexual and reproductive health in children, adolescents and young adults exposed to family violence.

•To explore sexual risk taking behaviour in children, adolescents and young adults exposed to family violence.

## Methods/design

### Trial design

This study is a randomized controlled trial using the method of minimization, as described by Taves (1974), to randomize the participants in two parallel groups with a 1:1 allocation ratio, being an intervention group, having access to “Feel the ViBe” + usual care (UC), and a control group, having access to minimally enhanced usual care (mEUC) [40,41]. Subcategories for the process of minimization will be sex (male or female) and age (12–17 years old and 18–25 years old). The study is conducted in the Netherlands. This trial is registered in The Netherlands National Trial Register (NTR) and assigned the trial ID NTR3692.

### Participants

For reading purposes, we will use ‘adolescent’ from now on to refer to the target group. The definition of ‘adolescent’ for this study protocol is: children, adolescents and young adults in the age of 12 to 25 years old. The study population consists of two age groups: 12–17 years old and 18–25 years old. We chose the age of twelve years old based on the common age in the Netherlands to start reproductive and sexual education and activities [42,43].

#### Inclusion criteria

Participants are adolescents in the age of 12–25 years old, exposed to family violence at home. Any adolescent encountering family violence at home, whether this is direct or indirect, is considered to be exposed to family violence.

#### Exclusion criteria

Since the internet-based self-support method is in Dutch, participants who do not speak the Dutch language are excluded. If, during the intervention period, a participant proves to be not a member of the target group, he/she is asked about the reason for his/her participation. The community manager will discuss this reasons anonymously with the supervising research team and decides if the participant is permitted to continue or will be excluded from further participation. In either case, his/her data are not being used in the evaluation.

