#### Recruitment and informed consent

Participants will be recruited both offline and online, by posters and flyers of the website “Feel the ViBe” spread amongst stakeholders in the field, general websites and social media to reach as many participants as possible. In this target group, internet literacy is assumed.

According to the principles of Dutch law, for participants age 12 to 16 years old, both parents (or guardians) must consent in addition to the minor him/herself. However, in cases of family violence, informing the abusive partner can be potentially dangerous, for both the abused parent and the adolescent exposed to the violence, and safety cannot be ensured. Therefore, in these cases we ask informed consent from the abused parent, being the mother in most cases, only.

Participants register themselves by sending an email to the community manager through the contact form online. In this early phase, inquiring participants about the type and severity of the violence would enlarge the threshold for participation. We therefore choose to consider every potential participant eligible as target group. If participants have read the patient information letter, available on the homepage, and have no further questions, they are eligible to participate and will receive a login name and password. On their first login, participants have to give informed consent electronically. If applicable, participants are requested to provide contact information of their parent(s), who then receive a unique code and a link to give consent as well.

The intervention is internet-based without face-to-face components. This means that participants are quasi-anonymous for each other. Having multiple identities is being prevented by making the registration a manual process, including a IP-address check and e-mail contact, and the informed consent process.

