Questionnaires	Measure outcomes and need to be filled out before accessing the elements behind login. Questionnaires will be activated in the personal menu. Questionnaires can be filled out one-by-one. Whenever possible, adaptive questioning is being used to make the burden as low as possible. There is a maximum of 15 questions per page. All items need to be filled out to submit a questionnaire. Participants cannot review their answers.	Available after first login, re-activated after 6,12, 18 and 24 weeks. *Element will no longer be obligated after trial.*
Personal menu	Menu for the participants with overview to all the available elements, access to the participants profile, digital testament, research information and contact information.	Login needed
User profile	The profile contains information on the participant, being: full name, nickname, avatar, sex, age, contact details and contact person. Only the nickname is available for other participants. The participant can choose a theme for the lay-out.	Login needed
Digital testament	The digital testament is required to fill out and lets participants choose how their data must be handled if they stop their participation.	Login needed
Ask the expert	Option to ask questions by e-mail to several experts, including a general practitioner, a sexologist, a psychologist and an expert in the field of family violence. Participants can also contact the community manager for general questions and questions regarding regular healthcare services. Response is given within 72 hours. During the RCT, this is the only available element for participants in the control group.	Login needed & questionnaires finished
Forum	The forum is meant to stimulate peer support. The community manager moderates the forum and stimulates contact. She will not intervene in the conversations except in case of offensive or factually wrong comments.	Login needed & questionnaires finished
Chat	Every two weeks we will offer a chat session for the participants with a specific theme and supported by an expert. Every other week there will be an unguided chat.	Login needed & questionnaires finished
Information	Information will be offered to the participants. Depending on the age in the profile, participants have access to tailored information about partner violence, sexual health, reproductive health, relations and healthcare. Participants are encouraged to discuss topics on the forum.	Login needed & questionnaires finished

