**Figure 1 F1:**
[figure not shown]
**Flowchart randomization procedure, received care and data collection.** Abbreviations: mEUC = minimally enhanced usual care, UC = usual care.

The intervention group will receive immediate access to “Feel the ViBe” after registration. Considering ethical concerns of withholding an intervention with a possible positive effect on physical and mental health, the control group will be a waiting list condition receiving minimally Enhanced Usual Care (mEUC) for twelve weeks before getting access to the intervention. mEUC is in general defined as non-study care enhanced in minor ways to address methodological or ethical issues. For this RCT mEUC is defined as Usual Care and access to a restricted version of “Feel the ViBe” offering only access to the user profile, consent forms, digital testament, research information, questionnaires and the “ask the expert” function to ask questions in case of emergency. Questions asked by members of the control group will not be answered by the Community Manager, but by one of the members of the Research Team who is not actively involved in the intervention, being author [name]. If help is needed immediately, the participant will be referred to his/her GP (Figure 1).

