### Randomization

Randomized trials with children and adolescents are controversial. The subject of our study enhances this even more. However to measure the effectiveness of an intervention, a randomized controlled trial is preferred above pre- post-test designs. Participants registering themselves online will be randomized to the intervention or the control group using the method of Minimization, as described by Taves (1974) [40,41]. Subcategories will be sex (male or female) and age (12–17 years old and 18–25 years old). This method minimizes the difference between the intervention and the control group. The allocation is carried out with help of a computer program by a research assistant.

Due to the nature of the study, participants cannot be blinded. Because of the nature of the overall study, containing both quantitative and qualitative parts, blinding of the investigators is difficult because the researchers need to know the group of the participant to be able to perform qualitative analysis and to follow each participant individually for the process evaluation. However questionnaires will be collected automatically during the trial in a SPSS file and delivered anonymized to the researchers.

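### Data of participants found after randomisation not to belong to the target group are dropped, and the intervention arm offers more opportunity to find them, above all in weeks 0 to 12

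*Protocol article*

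**What the plan says.** All references are to the protocol article.

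- **Entry (Recruitment and informed consent).** Type and severity of violence are deliberately not asked about at registration: "We therefore choose to consider every potential participant eligible as target group".
- **Allocation (Randomization).** "Participants registering themselves online will be randomized to the intervention or the control group using the method of Minimization".
- **Exclusion (Exclusion criteria).** The trigger comes later: "If, during the intervention period, a participant proves to be not a member of the target group". The participant is asked why he or she took part, and then: "The community manager will discuss this reasons anonymously with the supervising research team and decides if the participant is permitted to continue". Whatever is decided about access, "In either case, his/her data are not being used in the evaluation".
- **Access by arm (Intervention and Table 1).** The intervention arm has the full site at once, including the forum moderated by the community manager and the chat. Controls wait twelve weeks for it. Of the ask-the-expert function, Table 1 says: "During the RCT, this is the only available element for participants in the control group". The text adds the profile, consent forms, digital testament, research information and questionnaires, and states: "Questions asked by members of the control group will not be answered by the Community Manager".
- **Other contact (Ethical and safety issues).** Either arm may email or telephone the community manager.
- **Blinding (Randomization; Discussion).** Participants are not blinded, and blinding of investigators is called difficult. Questionnaire results reach the researchers only when the trial ends.

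**The concern.** Removing ineligible participants after randomisation can be harmless if eligibility is a baseline fact, established in the same way in both arms by someone who does not know the arm. The protocol requires none of this. Non-membership comes to light during the intervention period, through contact with the site or the staff, and the amount of such contact is what the trial randomises. If non-members are removed more often from one arm, the analysed groups are no longer the randomised groups, and the between-group comparison carries a difference in composition that the treatment did not cause. The rule is stated outright, so following the protocol as written produces the problem.

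**Working it through.** The protocol gives no figure on this point: no expected share of non-members and no detection rate. Only the 50 per group (Sample size) and the timings of access and measurement come from it. Everything else below is assumed and only illustrates scale.

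**1. Opportunity for detection.**

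| Period | Intervention arm | Control arm |
|---|---|---|
| Weeks 0 to 12 (to t = 2) | forum, chat, ask-the-expert, email, telephone | ask-the-expert (answered by another team member), email, telephone |
| Weeks 12 to 24 (to t = 4) | full site | full site |

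Questionnaire answers cannot even this out during the trial, because staff do not see them until the end.

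Suppose detection happens only through full access, with a constant weekly chance w and no attrition. By week 12 controls have zero detection. By week 24 the ratio of intervention to control detection is

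[1 − (1 − w)^24] / [1 − (1 − w)^12] = 1 + (1 − w)^12.

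At w = 1% this is 0.214/0.114 = 1.9; at w = 10% it is 0.920/0.718 = 1.3. Detection is therefore close to one-sided in weeks 0 to 12, and unequal but not one-sided over the whole follow-up.

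**2. Shift in follow-up means, all non-members found in the intervention arm and none in control.** Let p be the share of non-members and D the amount, in SD, by which they score lower. The intervention mean rises relative to control by p × D:

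- 0.05 × 0.5 = 0.025 SD
- 0.10 × 1.0 = 0.10 SD
- 0.15 × 1.0 = 0.15 SD

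**3. Partial detection.** If a share q of non-members is found in an arm, the share left among those analysed there is r = p(1 − q) / [p(1 − q) + 1 − p]. The shift is (r control − r intervention) × D. Example with p = 10%, D = 1 and detection of 80% v 0%: r intervention = 0.02/0.92 = 0.022 and r control = 0.10, so the shift is 0.078 SD.

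| p (D = 1 SD) | 80% v 0% | 80% v 40% | 80% v 80% |
|---|---|---|---|
| 5% | 0.040 | 0.020 | 0 |
| 10% | 0.078 | 0.041 | 0 |
| 20% | 0.152 | 0.083 | 0 |

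For D from 0.5 to 1.5 SD, the 80% v 0% column spans 0.02 to 0.23 SD. Numbers analysed in that case are 50 × (1 − 0.8p) = 48, 46 or 42 in the intervention arm, against 50 in control.

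**4. Change from baseline.** The Data analysis section plans ANOVA with between-group and within-subject effects. A stable low level is already present at t = 0 and cancels in a change score. Suppose members improve by a in the intervention arm and by b in control, and non-members, with little room to improve, change by 0.

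- All kept: (1 − p)a − (1 − p)b.
- Non-members removed from the intervention arm only: a − (1 − p)b.
- Difference: p × a, in favour of the intervention whenever its members improve.

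In step 2 the shift runs against the intervention, because its low scorers are removed. In step 4 it runs the other way. The sign depends on the contrast and on how non-members behave.

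**The case against.** A reader might infer four stronger statements that the protocol does not support.

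- **That non-members can be found almost only in the intervention arm.** This is fair for weeks 0 to 12 but not for the whole trial. Controls get the full site after week 12, can be identified then, and would lose all their data, including those up to t = 2. Before that they have ask-the-expert, email and telephone. The protocol does not define the intervention period for the control arm. It also does not say how someone proves to be a non-member. Age is one part of membership and is in the profile that both arms complete, so that route is symmetric.
- **That the community manager decides who is analysed.** The stated decision concerns continued access, after anonymous discussion with the research team, and the data go unused either way. Removal is also not driven by questionnaire scores, which the manager does not see. What remains is that someone must judge that a participant is a non-member, and nothing keeps that judgement blind to arm; anonymous discussion hides identity, not necessarily allocation.
- **That the bias runs against the intervention.** Step 4 of the working shows that it may run the other way.
- **That the shift can be set against a planned effect of d = 0.7.** The Sample size section gives 0.7 as the smallest effect in four earlier studies and does not adopt it as a planned effect.

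These objections limit the claim but leave its core. The exclusion occurs after randomisation, rests on information that emerges after allocation, and is applied where the arms differ in contact during the only randomised comparison with control.

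**Conclusion.** The point holds in this limited form: a post-randomisation exclusion, with no stated blinding to arm and more opportunity for detection in the intervention arm, above all before week 12. Its size and direction cannot be established from the protocol. About 0.03 to 0.15 SD in follow-up means rests on three assumptions: 5 to 15% non-members, a gap of 0.5 to 1.0 SD, and detection in the intervention arm only. With 40% detection in control against 80% in the intervention arm the shift is roughly half that under 80% against none, and with equal detection it is zero. The likely effect is modest, but the defect is written into the rule and is cheap to remove, so the rule should be changed.

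**What to change.** In Exclusion criteria, replace the sentence that removes the data with a rule to this effect: all randomised participants who gave consent remain in the primary between-group comparison, whatever is later judged about their membership of the target group. Decisions on continued access stay as they are.

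Exclude non-members only in a sensitivity analysis, using information recorded at or before t = 0 and available equally in both arms, judged by someone unaware of allocation. Age in the profile would qualify. Exposure would qualify only if t = 0 records it; none of the instruments listed under Outcomes is said to do so, and an item may have to be added.

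The cost is a change of wording for the primary analysis, slight dilution from a few ineligible participants in both arms, and possibly one extra t = 0 item for the sensitivity analysis. With everyone kept, this rule contributes no bias at any share of non-members. The Data analysis section separately drops anyone with fewer than five visits; the new sentence does not settle that rule and would have to be reconciled with it.
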